#### 1234 ***Assessment of Intensity***

1235 The investigator will make an assessment of intensity for each AE and SAE reported during  
1236 the study. The assessment will be based on the investigator's clinical judgement and  
1237 assigned to one of the following categories:

1238 Mild: An event that is easily tolerated by the participant, causing minimal discomfort and not  
1239 interfering with everyday activities.

1240 Moderate: An event that is sufficiently discomforting to interfere with normal everyday  
1241 activities.

1242 Severe: An event which is incapacitating and prevents normal everyday activities.

1243 An AE that is assessed as severe should not be confused with an SAE. Severity is a  
1244 category utilised for rating the intensity of an event; and both AEs and SAEs can be  
1245 assessed as severe. An event is defined as "serious" when it meets one of the pre-defined  
1246 outcomes as described.

#### 1247 ***Assessment of Causality***

1248 A blinded assessor will assess the relationship between study treatment and the occurrence  
1249 of each AE/SAE. The blinded assessor will use clinical judgment to determine the  
1250 relationship. Alternative causes, such as natural history of the underlying diseases,  
1251 concomitant therapy, other risk factors, and the temporal relationship of the event to the  
1252 treatment period will be considered.

1253 The causal relationship to the study treatment will be assessed using the following  
1254 classifications:

1255 Not Related In the Assessor's opinion, there is not a causal relationship between the study  
1256 product and the adverse event.

1257 Unlikely The temporal association between the adverse event and study treatment is  
1258 such that the study treatment is not likely to have any reasonable association  
1259 with the adverse event.

1260 Possible The adverse event could have been caused by the study treatment.

1261 Probable The adverse event follows a reasonable temporal sequence from the time of  
1262 study treatment, abates upon discontinuation of treatment and cannot be  
1263 reasonably explained by the known characteristics of the study participant's  
1264 clinical state.

1265 Definitely The adverse event follows a reasonable temporal sequence from the time of  
1266 study treatment start or reappears when study treatment is reintroduced.

1267 ***Assessment of Expectedness***

1268 **Expected** An adverse event, the nature or severity of which is consistent with the clinical  
1269 condition of the participant.

1270 **Unexpected** An adverse event, the nature or severity of which is not consistent  
1271 with the clinical condition of the participant.

1272 ***Follow-up of AEs and SAEs***

1273 All AEs and SAEs documented at a previous visit/contact and are designated as ongoing,  
1274 will be reviewed at subsequent visits/contacts.

1275 All AEs and SAEs will be followed until resolution, until the condition stabilises, until the  
1276 event is otherwise explained, or until the participant is lost to follow-up.

1277 New or updated information will be recorded on the originally completed SAE form, with all  
1278 changes signed and dated by the investigator.

1279

1280 **c. HANDLING OF WITHDRAWALS**

1281 If a participant experiences some distress as a result of participation in the study, and  
1282 decides to withdraw, we will offer them counselling or other appropriate support by staff who  
1283 are not members of the research team. No follow-up is required if a participant decides to  
1284 withdraw because of a lack of motivation or interest.

1285

1286 The investigator will inform each participant *prior to consenting* that data collected about  
1287 them up to the point of their withdrawal will be kept for the length of time specified by  
1288 department protocol (i.e., 7 years for demographic and cognitive data; 10 years for blood  
1289 samples), and will be included in all analyses. This is specified in the PICF and will be  
1290 highlighted by the recruiters. However, withdrawals will be handled on a case-by-case basis  
1291 – if a participant would prefer that we destroy their data and/or exclude their data from any  
1292 analysis, we will certainly consider their request. If a participant is unable to be contacted,  
1293 their data will be kept and included in all analyses.

1294

We will document in the research record each instance of a participant's withdrawal from the study, along with the following details: whether the withdrawal was initiated by the participant; the reason for their withdrawal, if known; and whether a request has been made to withdraw their data.

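### Section 7.b sets a weaker test for *Definitely* related than for *Probable*, so the top two causality grades are out of order and overlap

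*Protocol*

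**What the plan says.** Under Assessment of Causality in Section 7.b, a blinded assessor grades each AE and SAE as *Not Related*, *Unlikely*, *Possible*, *Probable* or *Definitely*, listed in rising order.

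The three upper grades are defined as follows.

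- *Possible*: "Possible The adverse event could have been caused by the study treatment". No timing, stopping or reintroduction criterion is attached.
- *Probable*: "Probable The adverse event follows a reasonable temporal sequence from the time of" "study treatment, abates upon discontinuation of treatment and cannot be" "reasonably explained by the known characteristics of the study participant's" clinical state. The three conditions are joined by 'and'.
- *Definitely*: "Definitely The adverse event follows a reasonable temporal sequence from the time of" "study treatment start or reappears when study treatment is reintroduced". The two conditions are joined by 'or'.

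The paragraph before the list applies to every grade. It says "The blinded assessor will use clinical judgment to determine the" relationship, and it lists matters to be weighed, beginning with "Alternative causes, such as natural history of the underlying diseases".

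**The concern.** On a graded causality scale, each step up should need at least as much evidence as the step below. Here the top grade needs less than the one beneath it. An event that begins at a plausible time after the programme starts meets *Definitely* even if it persists after exercise stops and the participant's condition explains it well. The same event fails *Probable* on two of its three conditions.

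This matters because the population makes such events foreseeable. Participants are about two months past an ischaemic stroke when the programme starts, and Section 7.b counts worsening of a pre-existing condition as an adverse event. Relationship to treatment is to be documented for each reportable event. Two assessors working from the same text, one following the definition and the other following judgment, could reasonably give one event different grades. Any later tabulation by causality would inherit that.

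**Working it through.** The protocol gives no figure to reproduce, so the check compares the two definitions as logical conditions. All inputs come from Assessment of Causality in Section 7.b.

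| Condition | *Probable* | *Definitely* |
|---|---|---|
| T: plausible timing after treatment | needed | enough alone |
| D: improves when treatment stops | needed | not mentioned |
| E: not explained by clinical state | needed | not mentioned |
| R: returns on reintroduction | not mentioned | enough alone |

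So *Probable* = T and D and E, and *Definitely* = T or R. Four yes/no conditions give 2 × 2 × 2 × 2 = 16 combinations.

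1. *Probable*: T, D and E are fixed and R is free, giving 2 combinations.
2. *Definitely*: all combinations except those with neither T nor R. These number 2 × 2 = 4, so 16 − 4 = 12.
3. Both grades: *Probable* requires T, and T alone meets *Definitely*, so both *Probable* combinations qualify: 2.
4. *Definitely* but not *Probable*: 12 − 2 = 10.
5. *Probable* but not *Definitely*: 2 − 2 = 0.
6. *Definitely* although the clinical state explains the event (E absent): T or R in 3 ways, D free in 2, giving 3 × 2 = 6 of the 12.

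Step 5 shows that the higher grade is strictly easier to meet. Step 3 shows that the two grades are not mutually exclusive: every *Probable* event also fits *Definitely*. Among the 10 in step 4 is the case of T alone, with no improvement, an adequate clinical explanation and no recurrence.

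Two simple repairs can be tested in the same way.

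- Changing 'or' to 'and' only: *Definitely* = T and R, which is met in 2 × 2 = 4 combinations. Only 1 of these also has D and E, so 4 − 1 = 3 would still be *Definitely* while failing *Probable*. This is not enough.
- Requiring everything: T and D and E and R, which is met in 1 combination. The order is restored, but an event that cannot improve or cannot recur could never be graded *Definitely*, however clear its cause.

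These counts describe the logic of the wording. They are not expected frequencies, because the combinations are not equally likely in practice.

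**The case against.** The strongest reply is that the definitions do not stand alone. A blinded assessor must use judgment and weigh the natural history of disease, concomitant therapy, other risk factors and timing before grading. *Not Related* rests on the assessor's opinion, and *Unlikely* is available where timing argues against a link. A sensible assessor would not call a well-explained event definite.

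This stands in part. It is why the defect is stated as what could happen on a literal reading, and not as what would happen. It does not cure the wording. The same paragraph directs the assessor to the listed classifications, and only *Probable* writes the alternative-explanation test into its definition. Judgment has to override the text of *Definitely* to reach the right answer.

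A reader might also infer three stronger things that the documents do not support.

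- **That the whole scale is inverted.** The three lower grades rise normally; only the top two are out of order.
- **That nearly every event in the exercise period would be graded *Definitely*.** There are 3 × 8 = 24 sessions, but the definition asks for a reasonable sequence and not merely onset during the programme. Session counts therefore say nothing about how many events would be misgraded.
- **That related-event counts become uninterpretable, or that ethics reporting is compromised.** Section 4.c lists no safety or relatedness outcome, and Section 8.c plans no analysis by causality. Section 7.b sends SAEs to the ethics committee yearly whatever their causality grade. Total AE and SAE counts do not depend on the grade. If *Probable* and *Definitely* were pooled, confusion between those two would not alter the count; only events moved up from lower grades would.

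Blinded causality assessment also limits the scope for bias between the arms.

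**Conclusion.** The point holds for the ordering and overlap of *Definitely* and *Probable* in Section 7.b. The higher grade has the strictly weaker test (12 combinations against 2, with 10 meeting *Definitely* only), and no other part of the protocol gives a definition that repairs it. The conclusion rests on reading 'and' and 'or' as written.

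The number of events that would be misgraded cannot be estimated from the protocol, because it depends on how far assessors follow the text over their own judgment. The consequence is confined to the causality grade and to any summary built on it. The statistical analysis plan is not at hand, so whether such a summary is planned there is unknown. The primary analysis, the sample size and SAE reporting are unaffected. This is a wording error in an operative safety classification. It should be corrected, but it does not threaten the trial's main conclusion.

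**What to change.** Reword *Definitely* in Section 7.b and on the adverse event form so that it is at least as demanding as *Probable* and the two grades cannot both apply. The sponsor may choose the wording, provided that:

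- plausible timing alone is not enough;
- the condition that the clinical state does not reasonably explain the event is carried over from *Probable*;
- reappearance on reintroduction counts as supporting evidence where it applies, and is not mandatory;
- one-off or irreversible events can still be graded. *Probable* itself requires improvement on stopping, so that condition should be worded in both grades to apply only where improvement can be observed;
- *Probable* is stated to cover events that meet its conditions but fall short of *Definitely*.

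The cost is a short text change and a revised form. Fewer events will reach the top grade. Any events already graded would need re-reading, for which the dates, action taken and outcome recorded in the CRF are a starting point. The design, schedule and participant burden do not change.

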#### d. REPLACEMENTS

As discussed below in Section 8.a (Power Calculations), we expect around 30% attrition due to death or non-participation (e.g., unable to participate in testing due to new pacemaker/implanted metal/other medical issue, lost to contact, not interested). This has been taken into account in our sample size estimation and power analysis, and so, the statistical significance of the sample size is unlikely to be affected by participant withdrawal.

## 8. STATISTICAL METHODS

#### a. SAMPLE SIZE ESTIMATION & JUSTIFICATION

We aim to recruit 120 participants who have experienced ischaemic stroke in the past 2 months. We calculate 60 participants per group are required. We calculated our sample size (see Section 8.b.) in order to include sufficient participant numbers for estimation of the primary endpoint: brain volume at 4 months post-stroke.

Methods of participant recruitment are detailed in Section 6.a.

#### b. POWER CALCULATIONS

The total sample size of 120 participants will yield 80% power to detect a difference corresponding to a medium to large effect size on brain volume measures, assuming the standard settings of 2-tailed significance,  $\alpha=0.05$ , and  $d=0.6$ . This effect size is reasonable, given that in our CANVAS pilot data, we reported hippocampal and total brain volume loss of -3% and -1.5% respectively over one year, in contrast to the control change of -0.4% and -0.6% over the same time period.

We have increased the sample size by 30% to cover attrition over the 12 month period and the possibility of non-evaluable scans (e.g., movement, etc.) giving  $n=60$  per group.

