### ***Emerging themes from the Cognition and Neocortical Volume After Stroke (CANVAS) study***

Researchers from the Alzheimer's Disease Neuroimaging Initiative (ADNI) study found that neurodegeneration, as measured by atrophy on MRI, both *precedes and parallels cognitive decline*, and concluded that serial MRI is the most useful modality for longitudinal dementia studies [8-9]. Brain volume loss after stroke has been controversial. It has only been with the advent of longitudinal studies that this progressive neurodegeneration has been documented *in-vivo*. The Melbourne-based Cognition and Neocortical Volume after Stroke (CANVAS) study, led by [name] [3], has been critical in describing these changes following stroke. The CANVAS study is a longitudinal study correlating cognitive performance and brain volume changes after ischaemic stroke [1, 3]. One hundred and thirty five participants with ischaemic stroke and 40 age- and sex-matched healthy control participants are tested on 4 occasions over 3 years with identical cognitive tests and advanced MR imaging. The primary hypothesis posits that change in regional and global brain volume between the 3 months and 3 year testing time-points correlates with cognitive performance.

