#### c. STATISTICAL METHODS TO BE UNDERTAKEN

The analysis can be considered in 3 parts, aligned with primary and secondary hypotheses:

- i. **Primary outcome and hypothesis: Comparing brain volumes between stroke participant groups:** Primary outcome will be analysed on an intention to treat basis, The difference in brain volume from baseline to 4 months will be analysed using an ANCOVA model with exercise intervention group as a factor (e.g., Physical fitness training vs. Balance training groups), with baseline brain volume and functional status as co-variants (dichotomised as mRS = 0-1, 2 and 3).
- ii. **Secondary outcome and hypotheses: Correlating brain volume with blood pressure control and incident stroke:** Secondary outcomes will be analysed using appropriate repeated measures random effect logistic regression models with dichotomised hypertension status or silent/recurrent brain infarction (as defined in methods) as dependent variables, treatment group as independent variable, and functional status dichotomized as a covariate (as above). The initial regressive analysis will examine the

differences between participants with good and poor blood pressure control, using this as a binary measure. The presence of incident subclinical stroke will also be included as a binary variable. In the regional volumetric analyses, total brain volume, regional white matter, cortical and subcortical grey matter volume changes will be modelled using this design.

- iii. **Exploratory analyses: Independent effects of exercise on blood pressure, incident stroke, diastolic cardiac indices, and aerobic capacity:** Exercise effects on end-organ function and fitness (i.e., aerobic capacity) are likely dissociable, however emphasise that this component is exploratory. For the purposes of these analyses, we define each of our end-organ metrics as: brain volume, cognitive function, incident stroke, diastolic cardiac indices, aerobic capacity (VO2max), sleep duration, onset latency, bedtime/rise time variability (minutes), and sleep efficiency (%). Exploratory analysis will be conducted using appropriate regression models to investigate the associations between BP, incident stroke, diastolic cardiac indices, aerobic capacity. In addition, mediation analyses will be conducted to explore the possible mediating role of sleep in preservation of brain volume.

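### Section 8.b: the step up to 60 per group covers a 25% loss rather than the stated 30%, and d=0.6 is supported only by a one-year stroke-versus-healthy difference that is not the contrast being tested

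*Protocol*

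**What the plan says.** Section 8.b claims that "The total sample size of 120 participants will yield 80% power to detect a difference" of medium to large size, using "2-tailed significance", alpha 0.05 and d=0.6. It then says "We have increased the sample size by 30% to cover attrition over the 12 month period". Unusable scans are to be covered by the same increase, which leads to 60 per group. Section 7.d expects about 30% attrition and says of it: "This has been taken into account in our sample size estimation and power analysis".

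The support offered for d=0.6 is the CANVAS pilot, where stroke patients showed "hippocampal and total brain volume loss of -3% and -1.5% respectively over one year". The corresponding losses reported for controls are 0.4% (hippocampus) and 0.6% (total brain). The background section on CANVAS describes its comparison group as "40 age- and sex-matched healthy control participants".

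The primary analysis is in section 8.c.i: "The difference in brain volume from baseline to 4 months will be analysed using an ANCOVA model". Exercise group is the factor there, and baseline brain volume and mRS category are covariates. The glossary places baseline at about 2 months post-stroke, so the primary interval is about 2 months.

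**The concern.** There are two separate issues.

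- **Attrition step.** Adding 30% to the required number does not protect against losing 30% of those randomised. Protection requires division by 0.7. Sections 7.d and 8.b both present the loss as covered.
- **Effect size.** The evidence for d=0.6 differs from the primary comparison in its groups (stroke versus healthy, against stroke versus stroke with both arms exercising) and in its interval (one year, against about 2 months). It also comes without an SD, so percentage losses cannot be turned into a standardised difference.

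The second issue matters more. If the primary result is null, readers will take it as 80%-powered evidence against a benefit of exercise. That reading depends on d=0.6 being plausible for this comparison, and the protocol gives no relevant ground for it.

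**Working it through.** **Inputs.** From section 8.b: d=0.6, two-sided alpha 0.05, power 80%, 30% increase, 60 per group, and the CANVAS one-year losses. From section 7.d: about 30% attrition. From section 8.c.i: ANCOVA of change from baseline to 4 months.

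**Step 1: reproduce the planned number.** Normal approximation: n per group = 2(1.96 + 0.842)² / 0.6² = 43.6, so 44. Two-sample t-test: 44.6, so 45. The protocol does not print this intermediate figure.
- Multiplying by 1.3: 44 × 1.3 = 57.2 and 45 × 1.3 = 58.5. Rounded up, this is consistent with 60.
- Dividing by 0.7: 44 / 0.7 = 62.9 and 45 / 0.7 = 64.3, so 63 to 65 per group (126 to 130 in total). This does not match 60.

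The plan therefore multiplied by 1.3.

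**Step 2: what 60 per group delivers at d=0.6.**

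| Evaluable per group | How reached | Power, t-test | Power, normal approx. |
|---|---|---|---|
| 60 | no loss | 90.3% | 90.8% |
| 46 | 60 / 1.3 | 81.2% | 82.1% |
| 45 | 60 × 0.75 (25% loss) | 80.4% | 81.2% |
| 42 | 60 × 0.70 (30% loss) | 77.6% | 78.5% |

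At 42 per group the shortfall against 80% is 2.4 points (t-test) or 1.5 points (normal approximation), and 80% power is reached at d=0.62.

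**Step 3: what the CANVAS figures can say about d.** The one-year gaps are 3 − 0.4 = 2.6 points (hippocampus) and 1.5 − 0.6 = 0.9 points (total brain). For both to equal d=0.6, the SDs would have to be 2.6 / 0.6 = 4.3 points and 0.9 / 0.6 = 1.5 points. Neither is stated. Even with SDs, the result would describe stroke against healthy over a year.

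**Step 4: illustration over 2 months.** Assume exercise removes the whole excess loss.
- Linear loss (assumption): 2.6 × 2/12 = 0.43 points and 0.9 × 2/12 = 0.15 points. For d=0.6 the SD of change could be at most 0.43 / 0.6 = 0.72 and 0.15 / 0.6 = 0.25 points.
- Half the yearly excess falling in this window (assumption): 1.3 and 0.45 points, with SD limits of 2.2 and 0.75 points.

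Suppose the SD of 2-month total brain change is 0.5 points (assumption, not in the documents), with 42 per group:

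| Timing of loss | Excess removed | d | Power (t-test) |
|---|---|---|---|
| Linear | all | 0.15 / 0.5 = 0.30 | 27% |
| Linear | half | 0.15 | 10% |
| Front-loaded | all | 0.45 / 0.5 = 0.90 | 98% |
| Front-loaded | half | 0.45 | 53% |

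The same SD gives anything from 10% to 98%.

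**Step 5: power at 42 per group for a smaller true d (t-test).** 62% at d=0.5, 44% at 0.4, 27% at 0.3.

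**The case against.** The case for the plan has four parts.

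- **The stated number is traceable.** The required sample was increased by 30%, and working back, 60 / 1.3 = 46 per group gives 81% power. This stands. A reader might infer that 120 participants match 80% power on no reading at all; the inflation reading shows otherwise.
- **The 30% may not apply at month 4.** Section 8.b ties it to 12 months of attrition plus unusable scans, and the background reports good retention in the predecessor study. With loss of 25% or less by month 4, 80% holds. This stands as a limit on the arithmetic point. It does not rescue the statement that a 30% loss is covered.
- **ANCOVA may recover the gap.** If d=0.6 is on the unadjusted scale, covariates correlating about 0.25 with the outcome raise d to 0.6 / √(1 − 0.25²) = 0.62, giving 80.1% at 42 per group. This also stands, but the protocol does not claim it.
- **d=0.6 is an openly stated assumption, and power is conditional on it.** True, so this is not a computational error. However, the protocol offers CANVAS as the reason the value is reasonable, and that reason does not fit the comparison.

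A reader might also infer from the illustrations that true power is as low as 10% or 27%. The documents do not support that. Those figures need an SD that is nowhere given and linear loss, whereas the background reports faster volume change than in controls within the first 3 months, a period that the trial interval partly overlaps. The front-loaded case under the same SD gives 53% to 98%.

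**Conclusion.** The point holds in two parts of unequal weight.

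**Attrition (minor).** The step to 60 per group covers up to 25% loss, not the 30% said to be covered. If the full 30% is missing at the primary endpoint, power at d=0.6 is 77.6% to 78.5% rather than 80%. Division by 0.7 would have given 63 to 65 per group. It would be too strong to say that the 80% claim fails outright: the shortfall depends on the full 30% being lost by month 4 and on no gain from covariates.

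**Effect size (the main point).** A one-year stroke-versus-healthy gap without an SD cannot support a standardised between-arm effect in stroke patients over about 2 months. Two different gaps, 2.6 and 0.9 points, are also offered for a single d. This rests on no outside figures, only on the protocol's own description of CANVAS and of its primary analysis. It does not show that d=0.6 is wrong or that the trial is badly underpowered. It shows that the value is unsupported and that true power cannot be determined from the documents.

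**What to change.** Section 8.b, with 7.d brought into line:

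- State the power by level of loss, for example: 60 randomised per group gives 80% power at d=0.6 if up to 25% are non-evaluable at 4 months, and 78% (80% at d=0.62) if 30% are.
- Remove the claim that the CANVAS stroke-versus-control contrast makes d=0.6 reasonable. Either label d=0.6 as an assumption, or support it with the between-arm difference expected in 2-to-4-month volume change and its SD from the team's serial scans.
- Show power over a range of d. At 42 per group it is 62% at 0.5, 44% at 0.4 and 27% at 0.3.
- In 7.d, replace the assurance that 30% attrition is already accounted for with a reference to the restated figures.

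The cost is a change of wording and, if the second option is taken, extracting an SD from existing scans. The stated power becomes less favourable. No extra participants and no design change are needed.
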